### Inclusion criteria

Children or young people under 18 years who:

Are admitted to paediatric critical care unit (PCCU).Have an acute illness including trauma.Have routine blood tests as part of their clinical care.

(or)

Children or young people under 18 years who are admitted to paediatric wards with confirmed COVID-19 illness or PIMS-TS.

### Exclusion criteria

Admitted to hospital for social reasons without an acute illness.Declined consent by parents or carers with legal responsibility, or by competent young person.Admitted to PCCU electively without an acute illness.Direct clinical care team not able to provide research information in a language appropriate for non-English/Welsh speaking participants.

### Patient/family journey

Any child or young person with an acute infectious illness or a non-infectious illness such as trauma on admission to PCCU will be eligible for participation in the study. All children will be screened by the direct clinical care team and research nurse. Research blood samples will be collected in those who are eligible. Data collected will include clinical and laboratory information essential for clinical characterisation including clinical profile, the severity of illness and clinical outcomes. There is no follow-up planned nor repeat blood samples following discharge from the hospital. Anonymous clinical data during the index hospital admission will be collected (figure 1).

**Figure 1 F1:**
[figure not shown]
Patient recruitment and blood sample analysis workflows. EDTA, Ethylene Diamine Tetra acetic Acid MS, mass spectrometry; PAXgene, Potassium Amyl Xanthate gene; PCCU, Paediatric Critical Care Unit; PIMS-TS, Paediatric Multisystem Inflammatory Syndrome Temporally related to SARS-CoV-2.

#### Research blood sample collection

Research blood sample will be collected at admission or onset of an acute illness in eligible children on PICU. In COVID or PIMS-TS patients on paediatric wards and who do not need intensive care, research blood samples will be collected once consent is obtained. Further blood samples may be collected but only alongside clinical blood samples and at least 24 hours apart during the illness, aiming to collect a final sample during recovery from organ failure. All research blood samples will only be collected along with blood samples required for routine clinical care.

#### Case definitions and group stratification criteria

We aim to retrospectively carry out deep clinical phenotyping of all patients recruited for the study using anonymous data from the case report forms (CRF) (online supplemental appendix 1). Two clinicians will review the data independently to allocate a diagnosis to all recruited patients. The allocation will be broadly into ‘infectious illness’, and ‘non-infectious illness’, with further categorisation into various specific illnesses including COVID-19 and sepsis (online supplemental appendixs 2 and 3—clinical phenotyping tool and clinical phenotyping flow chart, respectively). In case of any disagreement among the two clinicians, a third clinician will provide a final decision. This forms the reference standard for classification of illness, to aid interpretation of research sample analysis results.

10.1136/bmjopen-2022-067002.supp1Supplementary data

10.1136/bmjopen-2022-067002.supp2Supplementary data

10.1136/bmjopen-2022-067002.supp3Supplementary data

The current practice is to isolate all children admitted to PCCU and wards until their SARS-CoV-2 PCR test result is known. Only those cases that meet the clinical phenotype of COVID-19 illness will be categorised as COVID-19.^29^ Patients who are coincidentally positive for SARS-CoV-2, but identified with other illnesses on clinical phenotyping, will not be categorised as COVID-19.

As the revisions to the definition of sepsis are pending, clinical phenotyping will be broadly based on the surviving sepsis consensus definition (2005). Patients will be included if they meet two or more criteria of SIRS, with at least one criterion related to white cell count or temperature, and with confirmed or strongly suspected to have an infection.^3^ There have been algorithms used previously to identify bacterial infections.^15 30^ In this study, we plan to evaluate sepsis due to any aetiology including fungal or viral infections. The clinical phenotyping will aid in categorising patients into descriptive clinical clusters, which we believe would have more utility in studying differences in immune-metabolic biological pathways between sepses due to viral, bacterial or fungal sepsis or where there is no microbiological agent identified. The process aims to report those cases as sepsis, which may deviate from the 2005 consensus definition, but have strongly suspected or confirmed infection and life-threatening organ dysfunction as described in the latest surviving sepsis consensus guidance statement.^4^ In addition, we can study the differences in sepsis as a whole in comparison with other acute illnesses. In those patients with confirmed infections and who do not meet the SIRS criteria for sepsis, deep clinical phenotyping will help us in evaluating the immune and metabolic markers based on patient outcomes such as severity of illness and organ dysfunction.

### Recruitment and consent

Recruitment of eligible children admitted to PCCU meets the criteria for emergency research as we need to collect research blood samples soon after admission to the critical care unit, along with routine blood tests and it would be inappropriate to approach parents or legal guardians for consent.^31^ We have ethics approval for research before consent and collection of multiple samples if the research team find parents not ready to make an informed choice to consent for research. Consultee advice will be sought in patients who are 16 and 17 years old who lack capacity or are not able to make an informed choice due to the critical illness.

In patients admitted to wards with confirmed COVID-19 or PIMS-TS, consent will be obtained after appropriate information sharing before research sample collection at the time of routine clinical blood sampling.

### Patient and public involvement

The study group have engaged with representative members of public for the design of the study. Specific areas where this has led to incorporation of ideas and feedback are listed below:

Justification for the Study: Early identification of severe infectious illness will provide a diagnosis and information on prognosis will help in counselling and communicating with patients, families and parents.Representatives of parents have approved of the methods involving research before consent as this is considered research in an emergency setting. The feedback stressed the importance of timing in the approach to parents of prospective research participants, to allow information sharing and consenting in such a way it causes minimum distress. We agreed that the timing for the approach should be based on the parent’s and patients’ ability to understand the research and not based on the duration from collection of first sample.In view of the importance of appropriate timing for informed consent, it was also agreed that we could take further samples before consent. This was only in a situation where the direct clinical care team and research nurses felt that the parents may be emotionally not ready for approach or prospective research participant was severely unwell.Representative members of the public were involved in drafting information sheets for parents, carers and older children. The final drafts were approved as appropriate for sharing information with parents and patients at the time of initial approach and consenting. Even though feedback about the information provided was incorporated, the information could not be shortened due to regulatory requirements.Feedback from patient groups through Wales Gene Park included the research methods and information shared with families and legal guardians. Also included specific information related to next-generation sequencing in the study. The feedback was supportive of the methods used and suggestions were incorporated into the information sheets.

Peer review and feedback were sought through the UK Paediatric Intensive Care Society—Study Group as well as during a previous grant application.

### Clinical data

CRF will be used for collecting anonymous clinical data, including the clinical classifier (figure 1) from clinical phenotyping (online supplemental appendix 1).

### Sample size calculation for transcriptomic analysis using RNAseq

We aim to recruit 250 patients with acute illnesses admitted to our PICU. Extrapolating the results of previous reports on the prevalence of severe sepsis in the paediatric intensive care population, we estimate that there will be around 25 patients with sepsis included in our study.^32 33^ For calculating the power and type 1 error (α), we refer to the negative binomial model for biological variability estimations in human samples used by Hart *et al*.^34^ Using an RNAseq minimum read depth of 30 million reads per sample and a liberal coefficient of variability (σ) of 0.6, we calculate that to achieve a Power(β) of 0.8 and type 1 error (α) of 0.01, we would need around 20 samples in each group for a twofold change in differentially expressed genes.

### Data processing and analysis

Paired-end reads from RNAseq Illumina sequencing will be trimmed and processed for quality control,^35 36^ before mapping to the human genome using Spliced Transcripts Alignment to a Reference.^37^ Once we have read counts per gene/transcript, we plan to use R Language and Environment for Statistical Computing^38^ followed by quality control and data processing using Bioconductor packages.^39^ A per-gene hypothesis of differential average expression will be tested using a negative binomial generalised linear model—DESeq2 package and resulting p values will be controlled for multiple testing using the Benjamini-Hochberg method.^40^ For classification, a variety of machine learning and statistical pathway biology approaches, as described in Smith *et al*,^10^ will be used. Pathway analyses will be carried out stepwise using a pathway biology approach, becoming more focused. For metabolomic and proteomic data, absolute concentrations (determined by LC-MS/MS) of analytes in extracts from blood samples will apply validated tools such as MetaboAnalyst V.4.0.^41^ Further multivariate statistical testing (Principal Component Analysis, Partial Least Squares Discriminant Analysis, Random Forest and Analysis of Variance) using group assignment derived from clinical phenotyping (types of sepsis and between sepsis and non-septic controls) will also be used to determine metabolites or proteins that are significantly different in abundance between clinical phenotypes. Single-cell analyses (CITE-Seq) using surface protein and RNA libraries (10× Genomics) and next-generation sequencing will be multiplexed by cell ‘hashing’.^42^ Demultiplexed sequencing data will be aligned to the reference transcriptome using CellRanger (10× Genomics) and the number of unique molecular identifiers per cell will be quantified. Computational analyses and quality control will be performed using R packages including Seurat to integrate hashtag, protein and RNA libraries while also enabling demultiplexing of donors, doublet detection and cell clustering.^43^

For the final pathway biomarker assessment of the predictive success of the model, Receiver Operator Characteristics will be applied.

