### Definition of sepsis in children

At present, sepsis is defined in adults as life-threatening organ dysfunction resulting from a dysregulated host response to infection.^2^ This definition has removed the terms ‘systemic inflammatory response syndrome’ (SIRS) and ‘severe sepsis’ found in previous definitions and highlights organ dysfunction for clinical management. In children, the existing surviving sepsis consensus conference definition of sepsis based on the criteria for SIRS in the presence of confirmed or suspected infection is still used for identification of sepsis and clinical research.^3^ The recently updated guidance for the management of sepsis in children (2020) recognises the clinical heterogeneity of this illness in children, accounting for life-threatening organ dysfunction.^4^ A revised definition of sepsis by the paediatric sepsis definition task force is awaited.^5^ Recently, we put forward a setpoint mechanism for understanding sepsis. This suggests that dysregulation of the host response to infection in sepsis is explainable by regulatory shifts in homeostasis setpoints. This is due to negative and positive feedback changes in the concerted behaviour of multiple (immune, metabolic and neuronal) systems in response to infection. We hypothesise that infants and children have age-dependent metabolic demands and a developing immune setpoint that increases the risk of sepsis.^6^ Sepsis can arise from any type of infection—bacterial, viral, fungal or parasitic.^4^ Even though less common in children, COVID-19 can be associated with severe illness. History of infection and age-dependent changes in the immune system give rise to subtle but important differences in response to SARS-CoV-2 infection in children when compared with adults. In the early life and younger years, the innate response is a dominant feature of the immune response to infection. In the case of SARS-CoV-2 infection, children are known to mount a stronger and more vigorous interferon (IFN) antiviral response than adults, curtailing viral replication at an early stage of infection.^7^

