## Methods

### Hypothesis and specific aims

A neonatal sepsis classifier integrating immune and metabolic pathways was able to discriminate neonates with bacterial infections and sepsis with high accuracy.^10^ We hypothesise that the integrative tripartite immune-metabolic pathways represented by differentially expressed genes between sepsis and other illnesses would discriminate bacterial infection causes of sepsis from COVID-19 illness and other acute non-infectious illnesses. The immune-metabolic pathways vary between different age groups in children under 18 years. Our specific aims include:

Compare immune and metabolic markers, which discriminate sepsis and COVID-19 from other acute non-infectious illnesses in children admitted to paediatric intensive care unit (PICU).Investigate the evolution of immune responses in children with sepsis and COVID-19 using serial samples.Evaluate the utility of gene expression markers to discriminate heterogeneous subgroups of sepsis and other critical illnesses with the help of deep clinical phenotyping.Understand physiological processes associated with COVID-19 and PIMS-TS and how they differ from bacterial sepsis aetiology.Explore age-dependent differences in systemic host response and determine whether these differences are associated with the risk of disease severity to infection.

We plan to explore the feasibility of objectively defining the balance between immune tolerance and resistance in general, as well as in different paediatric age groups. This is through investigating pathway biology response to sepsis and multiomic analyses.

This is a prospective cohort study with a nested case–control analysis. The start date was 30 June 2020 and the proposed end date is 01 June 2023.

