## Discussion

Through this prospective observational cohort study, we plan to evaluate immune-metabolic biological pathways in children with acute illnesses admitted for paediatric critical care. The aim is to evaluate the differences in immune and metabolic pathways in children with sepsis and other illnesses including COVID-19 in children and young people. The use of the cohort design will help in recruiting children of different age groups from birth to under 18 years admitted to PCCU with acute illnesses. The subsequent nested case–control analysis of different clinical groups from the cohort matched for age will help to identify differentially expressed genes among the different clinical phenotypes such as COVID-19 and sepsis with microbiological confirmation, COVID-19 and other viral infections, PIMS-TS and viral infections, PIMS-TS and sepsis with microbiological confirmation, sepsis with microbiological confirmation and confirmed viral infection. The initial analysis in a discovery cohort will be followed by cross-validation in a subsequent validation cohort. Feedback from parents and patient representatives has highlighted the importance of paediatric research for early identification of infections with subsequent poor outcomes or need for organ support. We hope that this study will help in planning future studies addressing this need. We plan to include children with polytrauma as this is considered an example of sterile inflammation.

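### Metabolites and proteins are compared by phenotype group with no age control stated, so an analyte that only tracks age may be reported as a disease marker

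*Protocol article*

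**What the plan says.** For the metabolomic and proteomic layers, the protocol article (Data processing and analysis) names the methods, "Principal Component Analysis, Partial Least Squares Discriminant Analysis, Random Forest and Analysis of Variance", applied "using group assignment derived from clinical phenotyping (types of sepsis and between sepsis and non-septic controls". The stated purpose is "to determine metabolites or proteins that are significantly different in abundance between clinical phenotypes". Age does not appear in that description.

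Age matching appears once, in the Discussion: a "nested case–control analysis of different clinical groups from the cohort matched for age will help to identify differentially expressed genes". Five example contrasts follow. They pair COVID-19, PIMS-TS, viral infection and microbiologically confirmed sepsis with one another.

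On age itself, Definition of sepsis in children hypothesises that "infants and children have age-dependent metabolic demands and a developing immune setpoint" raise the risk of sepsis. Hypothesis and specific aims says: "The immune-metabolic pathways vary between different age groups in children under 18 years". One of the specific aims is to explore age-dependent host response.

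**The concern.** Confounding by age needs two links: age with analyte, and age with group. The protocol asserts the first. It makes the second plausible. Its section on COVID-19 in intensive care lists age over 10 years as a risk factor for severe disease. Its Introduction gives very different sepsis incidences for neonates (2202 per 100 000 livebirths) and children (48 per 100 000 person-years). Those denominators differ and the figures are for populations, not for this unit, so they show only that sepsis is patterned by age.

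If the compared groups do differ in age, an analyte with no disease effect will differ in mean between them. Benjamini-Hochberg or any other multiplicity correction does not help, because the difference in means is real; only its attribution to disease is wrong. Such an analyte could then enter the immune-metabolic network that the study sets out to build. The exposed comparison is sepsis versus non-septic controls, which serves the first specific aim.

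**Working it through.** **1. What is fixed for each layer.**

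| | Gene expression | Metabolites and proteins |
|---|---|---|
| Model named | Negative binomial GLM (DESeq2) | PCA, PLS-DA, Random Forest, ANOVA |
| Age term in the model | None stated | None stated |
| Age matching | Stated in the Discussion | Not stated |
| Contrast with a non-infectious arm among the matched examples | None of five | Not applicable |

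The matching sentence gives genes as its output, and its examples supply no matched set for sepsis versus non-infectious illness. The Discussion says children with polytrauma will be included as an example of sterile inflammation, but attaches no matched contrast to them.

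**2. Group sizes for an illustration.** The protocol's RNAseq figure of about 20 per group reproduces: n = 2(2.576 + 0.842)² × (1/μ + 0.6²)/(ln 2)². The mean count per gene μ is not stated; the result is 19.9 at μ = 20, 19.1 at μ = 30 and 18.5 at μ = 50 (two-sided). This calculation does not cover metabolites or proteins and is used only to set a plausible matched size. The unmatched extreme is about 25 sepsis cases against 250 − 25 = 225 others.

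**3. Error rate when age is left out.** Take an analyte with no disease effect, within-group correlation r with age, and groups d within-group SDs apart in mean age. Neither r nor d is in the document; both are assumed. The unadjusted test statistic is shifted by m = r·d/√(1/n₁ + 1/n₂), and the two-sided rejection rate is Φ(−1.96 + m) + Φ(−1.96 − m).

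For r = 0.5 and d = 1:
- 20 v 20: m = 0.5/0.316 = 1.58, rate 0.353.
- 25 v 225: m = 0.5/0.211 = 2.37, rate 0.660.

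| r | d | 20 v 20 | 25 v 225 |
|---|---|---|---|
| any | 0 | 0.050 | 0.050 |
| 0.3 | 0.25 | 0.056 | 0.065 |
| 0.3 | 0.5 | 0.076 | 0.110 |
| 0.5 | 0.5 | 0.124 | 0.220 |
| 0.3 | 1.0 | 0.158 | 0.296 |
| 0.5 | 1.0 | 0.353 | 0.660 |

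Simulation (4000 runs per setting) for (r, d) = (0.3, 0.5), (0.5, 0.5) and (0.5, 1.0) gave unadjusted rates of 0.071, 0.128 and 0.335 at 20 v 20, and 0.107, 0.210 and 0.644 at 25 v 225. With age in the linear model, all six settings lay between 0.046 and 0.055.

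**4. What adjustment costs.** With equal groups, adding age multiplies the standard error of the group effect by √(1 + d²/4), before any gain from age explaining analyte variance. That is 1.12 at d = 1, 1.25 at d = 1.5 and 1.41 at d = 2.

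**5. Why not residualise on age first.** Regressing the analyte on age across pooled groups, then comparing residuals, leaves a fraction 1/(1 + d²/4) of a true group difference at equal sizes: 64% at d = 1.5 and 50% at d = 2. Real disease signal would be lost.

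**The case against.** The strongest reply is that this is partly read from silence. A reader might infer that the metabolic half of the study has no age control and that age differences will be published as disease markers. The documents do not support that. No sentence says that the metabolite comparison uses the unmatched cohort or omits age, and a condensed article may leave covariates to an analysis plan that is not shown. Methods describes the whole study as a cohort with a nested case–control analysis. The Discussion's wording, "The subsequent nested case–control analysis of different clinical groups from the cohort matched for age", matches groups of children, who could supply metabolite and protein data as well as RNA. The contrast list is introduced as illustrative. The gene model has no stated age term either, so it is also too strong to infer that the two layers will certainly estimate different things.

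Most of this stands, and it limits the point to what is stated and what may follow. It does not remove it. The article does address age control, and where it does, the stated output is that it "will help to identify differentially expressed genes among the different clinical phenotypes". For the other layers it fixes methods, grouping variable and purpose without age. Matched children could be used, but no matched set with a non-infectious arm is described.

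The objection is also right that the error rates rest on assumptions, and that 25 versus 225 presupposes an unmatched comparison. No section shows that septic and non-septic children in this unit differ in age.

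**Conclusion.** The point holds as a conditional one. Followed as written, the metabolite and protein analysis leaves the sepsis versus non-septic comparison open to confounding by age, in a cohort where the protocol itself expects age to matter. Bias arises only if the compared groups differ in age and the analyte depends on age. The document quantifies neither, so the size is unknown. Under the assumed values tabulated, a nominal 5% error rate ranges from no inflation to 35% at 20 versus 20 and 66% at 25 versus 225. These are illustrations and not predictions.

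This merits a change to the analysis and not just a clarifying sentence, because ANOVA by group has a better alternative at almost no cost. Unequal variances between groups are a secondary matter and form no part of the conclusion.

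**What to change.** In Data processing and analysis:

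- Replace ANOVA by group with a per-analyte linear model on log concentration, with phenotype group plus age (spline or age bands). A heteroscedasticity-robust standard error is optional.
- Keep sepsis versus non-septic controls as a contrast. Restricting every layer to the Discussion's example contrasts would drop the non-infectious comparison that the first aim needs.
- Run PLS-DA and Random Forest on age-matched sets that include non-infectious controls, and not on pooled age-residualised data.
- State in the Discussion that the age-matched design covers metabolites and proteins as well as genes.
- Report the age distribution of each compared group. Where overlap is small, say that the adjusted estimate is imprecise and leans on extrapolation.

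The cost is slightly more analysis work, a few degrees of freedom for age, and some loss of precision, which becomes material where ages barely overlap. Age should be known for every child, so no new samples or data are needed.
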